**Fig. 1 Fig1:**
[figure not shown]
Algorithm of the decision aid

Non-health care professionals do not perform a suicide risk assessment as they are not authorized to do so. When they signal a person at risk for suicide, the risk assessment will be performed in the SMHI, in the same manner. The monitoring system also provides follow-up care from the SMHI, which is described in pillar 2, 3 and 4.

### Pillar 2: providing swift access

Providing swift access to people registered in the monitoring system by specialist crisis teams of SMHIs is the second pillar of our intervention. The first time period after someone showed suicidal behavior remains very vulnerable for relapse, as suicide occurs mostly in people not receiving mental health care [7, 8] and in transitions of and discharges from care [10, 11]. But although suicide risk is thirty times higher in people with a previous attempt [1], one attempt may not necessarily be followed by another one, if proper mental health care is provided after the attempt. Suicide risk can also abate after a failed attempt. Out of 515 patients who attempted suicide at the Golden Gate Bridge, 94% did not die from suicide, at a 26 years follow-up [28]. Moreover, it has been found that appropriate pharmacological or psychotherapeutic treatment may prevent suicide [15, 29]. A recent systematic review and meta-analysis indicated that suicide prevention interventions were found to be effective in preventing completed suicides [30]. Providing swift access to people identified with suicidal behavior to specialist mental health care is thus highly desirable. In this study, swift access will be facilitated by the monitoring system and will be provided by the SMHI. In case a persons’ suicidality is not mainly caused by a psychiatric disorder, but for example, due to financial or somatic problems, the person might be referred to other (health) care settings if that is more appropriate.

### Pillar 3: positioning nurse care managers according to collaborative care

The third pillar of our intervention is the positioning of nurse care managers to collaborate with psychiatrists in assessment, case management, and guidance to treatment according to the collaborative care model. Collaborative care is an intensive care model that involves a number of health care professionals working together, such as a medical doctor, a case manager, and a psychiatrist. The case manager has regular contact with the person and organizes care, together with the medical doctor and specialist, and may offer help. There is ample evidence worldwide that collaborative care is successful in the treatment of depression [31–35]. Collaborative care has also been shown to be feasible, acceptable and effective in the prevention and reducing suicidal ideation [29]. A Cochrane review indicated that the implementation of treatment guidelines succeeds better if nurses are trained with that purpose [36]. In this study, collaborative care will be embedded in pillar two and four. Nurse care managers will collaborate with the person and his/her psychiatrist, clinical psychologist and general practitioner in suicide risk assessment, providing swift access to treatment, and monitoring. They will also signal potential problems in the continuity of care and will communicate this with the involved professionals.

### Pillar 4: providing one-year telephone monitoring

Providing telephone monitoring at five fixed times during 1 year to people registered in the monitoring system to enhance adherence to treatment is the fourth pillar of our intervention. The first year after a person showed suicidal behavior, usually many transitions within (mental) health care settings occur. The risk of suicide is increased during these transitions, as it has been found that of those who have died by suicide and were previously receiving mental health care, 24% were discharged in the previous 3 months. Most of these suicides already occurred in the first week after discharge [37]. Often there was non-compliance with treatment and loss of contact with services prior to the suicide [37]. This might be due to the lack of long-term monitoring follow up of people at risk for suicide. Multiple reviews already reported that structured follow-up contact with high-risk individuals, such as people that attempted suicide, decreased future suicidal behavior [11, 29]. Cebriá et al. (2013) found in a randomized controlled trial that providing patients at a general hospital emergency room that had attempted suicide with appropriate care and telephone follow up reduced the rate of patients reattempting suicide by 8%, compared to care as usual [38]. In our study, a one-year telephone follow-up care is provided to the people registered in the monitoring system. This follow-up aims to monitor the suicide risk and the continuation of care and is provided by the SMHI. The SMHI professional will signal any problems in the monitoring contact, and will communicate this with the clinician or general practitioner and will arrange new appropriate care if needed.

### Target population

The target population for the intervention are people that present themselves to, or are identified by, a professional of one of the participating institutions by showing signs of suicidal behavior. In this study, suicidal behavior includes both suicidal ideations and actions -preparatory and attempting- that are undertaken with the intention to die [17]. Inclusion criteria for registration in the monitoring system are 1) having a medium to high suicide risk according to the decision aid (see paragraph ‘Framework’ for the decision aid), 2) being a resident of the province of Noord-Brabant, and 3) giving permission to be registered in the monitoring system. People will be excluded if 1) low suicide risk is assessed, 2) they are not living in Noord-Brabant, and/or 3) they do not give consent to be registered in the monitoring system.

### Procedure of the intervention

The procedure of SUPREMOCOL is divided into three steps. In the first step, a person with suicide risk is registered in the monitoring system. A first contact with the crisis care manager is performed after registration, which is the second step in the procedure. In the third step, follow-up monitoring is provided to the people registered in the monitoring system. The four pillars of SUPREMOCOL are embedded in all steps.

### Step 1: registration in the monitoring system

In our systems intervention, both (mental) health care professionals - such as emergency room physicians, general practitioners or school psychologists - as well as non-health care professionals - such as railway professionals - can signal people at risk and register them in the monitoring system. When participating professionals signal people at risk, they first ask them for permission for registration in the monitoring system (according to the European Union General Data Protection Regulation [GDPR]). When permission for processing personal data is given, professionals who work as a (mental) health care professional perform a suicide risk assessment via the decision aid, which is built-in the monitoring system. The decision aid provides feedback based on the input provided by the persons’ answers on a questionnaire and observations made by the professional. If the suicide risk is *low* according to the decision aid, the person will not be registered and the professional is advised to refer the person to his/her general practitioner. If the suicide risk is *medium* or *high*, the person will be registered in the monitoring system, and their registration is automatically sent to the nearest SMHI, this is based on the postal code of the person who will be registered. Professionals that do not work in (mental) health care do not perform a suicide risk assessment as they are not authorized and trained to do so. They will register people in the monitoring system based on their own estimation. In these cases, the risk assessment will be performed later on by the SMHI crisis care professional who can use the decision aid to do so.

### Step 2: first contact with the crisis care professional

The (daily) check for new enrolments in the monitoring system is conducted by crisis care professionals from the SMHI. This professional will actively seek contact on a daily basis with the people registered. They will check if a crisis assessment is necessary and they will ensure that these people receive swift access to appropriate care, most probably in the SMHI itself. SMHI professionals will work according to the collaborative care model by collaborating with the person and the involved professionals during 1 year. A flowchart of the first contact is provided in Fig. 2 .

**Fig. 2 Fig2:**
[figure not shown]
Flowchart of the first contact

### Step 3: follow-up monitoring

Telephone follow-up monitoring will be systematically provided for one-year to monitor suicide risk and the continuity of care by the SMHI professional in close collaboration with psychiatrists. The monitoring contacts take place at five fixed times, i.e. 6 weeks after registration in the monitoring system, and after 3, 6, 9 and 12 months. In the monitoring contacts, the suicide risk will be assessed and the person will be asked if he/she is receiving SMHI care. If the person *is* receiving SMHI care, and the suicide risk is low, their clinician will be informed by mail about the suicide risk assessment or the person will be advised to inform their clinician him/herself. In case of a high suicide risk, the clinician will be immediately informed by phone. If the person is *not* receiving SMHI care, and the suicide risk is low, their general practitioner will be informed about the suicide risk assessment. If the suicide risk is high, the crisis care manager will again arrange swift access to appropriate care. A flowchart of follow-up monitoring is provided in Fig. 3.

**Fig. 3 Fig3:**
[figure not shown]
Flowchart of the follow-up monitoring

### Setting

The intervention will be implemented in Noord-Brabant, one of the twelve provinces of the Netherlands. Noord-Brabant comprises an area of over 5000 km^2^, about 2.5 million inhabitants and five specialist mental health institutions. Institutions can participate in the intervention if they signal residents of Noord-Brabant at risk for suicide. We will involve as many settings as possible that can identify people at risk for suicide [39]. Therefore, we do not only include mental health care institutions but organizations in all other settings that might participate by signaling people at risk for suicide. Examples are general hospital emergency rooms and psychiatric departments, general practitioners, occupational physicians, youth mental health care, schools, municipal services, and railway services. All relevant institutions in Noord-Brabant will be approached for participation by the researchers, but when interested, institutions can also contact the researchers themselves. New chain partners may be identified and included during the project. A list of participating organizations can be obtained via the authors.

### Step-wise implementation

The intervention will be stepwise implemented in five subsequent subregions of the province of Noord-Brabant until eventually the system is implemented in the whole province. In the time periods and subregions in which the region is not allocated to the intervention conditions, care as usual is provided. Further details about the stepwise implementation are discussed in paragraph ‘Study design’.

### Scientific evaluation

#### Hypotheses

It is hypothesized that SUPREMOCOL will lead to a reduction of completed suicides of 20% in the province of Noord-Brabant, both in time and compared to the other provinces. Moreover, it is hypothesized that SUPREMOCOL will lead to less completed suicides and suicide attempts, both in association with the stepwise implementation of the system intervention in the subregions of the province, and will diminish suicidal ideation in people registered in the monitoring system.

#### Study design

The design of the SUPREMOCOL study comprises three elements: 1) a stepped wedge trial design, 2) a public health impact evaluation by the RE-AIM framework and 3) an intervention integrity evaluation.

### Stepped wedge trial design

The SUPREMOCOL intervention will be evaluated in a stepped wedge trial design (SWTD). In a SWTD, an intervention is sequentially rolled-out to a group of clusters. A cluster is a group of participants that operate in the same geographical area. In our study, a cluster is a specialist mental health care institution together with a group of participating general practitioners, hospitals, and other organisations that operate in that particular SMHI area. We chose a SWTD for ethical, scientific and practical reasons, as further discussed in the ‘Discussion’ of this paper. Stepped wedge trials comprise three main phases: the pre-rollout period, the rollout period and the post-rollout period [40, 41]. In period 0, the so-called pre-rollout period, the intervention has not been implemented in any of the clusters. Next, there will be a rollout period during which clusters are crossing over from the control condition (in this study care as usual) to the intervention (SUPREMOCOL). In period 1, the intervention will be implemented in cluster 1, while the other clusters will keep providing care as usual. In period 2, the intervention will also be implemented in cluster 2 (cluster 1 will still be included), while the other clusters will keep providing care as usual, and so on. In the post-rollout period, the intervention will be implemented in all clusters. A schematic representation of the present SUPREMOCOL trial is given in Fig. 4. Each cell represents a time period and a certain cluster and includes a data collection point. Blank cells represent control periods and shaded cells represent intervention periods [41, 42].

**Fig. 4 Fig4:**
[figure not shown]
Sequential rollout of the suicide prevention system (shaded cells) to the clusters

In our SWTD, the implementation of SUPREMOCOL is sequentially rolled-out to five clusters, until eventually the system is implemented in the whole province. For this purpose, the province is divided into five sub-areas that are based on the service areas of the five participating SMHI’s. The SMHI and a few participating organizations are exposed to the experimental condition from the start of their cluster, but at various time points, more organizations in that cluster may participate if they sign up for participation [40].

### Public health impact evaluation

The public health impact of the SUPREMOCOL intervention will be evaluated, as previous studies found that it is important to not only assess the efficacy of an intervention but to also evaluate its impact [43]. For example, an intervention might be very successful in an optimal and controlled experimental condition but might have poor implementation outcomes in complex real-world settings [43]. As a result, many interventions that were found to be effective were never widely adopted in practice [44]. The evaluation to the public health impact of SUPREMOCOL will be done in terms of the five dimensions - Reach, Efficacy, Adoption, Implementation, and Maintenance - of the RE-AIM framework [43]. *Reach* refers to the extent of participation, on an individual level. It can be measured by calculating the rate of the numerator (participants) versus the denominator (population). Additionally, the representativeness of the participants can be assessed by evaluating their characteristics [43]. In this study, reach is the level in which SUPREMOCOL is used by the target population (both patients and professionals) and to their characteristics. *Efficacy* refers to the positive and negative consequences of the intervention and to behavioural and participant satisfaction outcomes [43]. In this study, changes in the outcome measures (suicidal behaviour), compliance with intervention procedures and experiences of patients and professionals with the system were measured to evaluate the efficacy of SUPREMOCOL. The proportion and representativeness of the settings that participate refer to the dimension *adoption* [43]. The level in which settings and professionals are willing to initiate the system, including their characteristics, are examined to measure this dimension in this study. *Implementation* is an individual- and intervention-level dimension and refers to the extent to which an intervention is delivered as intended [43]. In this study, implementation is defined as the level in which the system is implemented according to the protocol. The last dimension is *Maintenance*, which refers to the extent to which the intervention is part of a long-term behavioural change in individuals and organisations and has reached a stable and enduring phase [43]. Maintenance is in this study examined by an evaluation of the long-term compliance with intervention procedures and by attrition analyses.

### Intervention integrity evaluation

Intervention integrity will be measured during implementation. This will be done to gain insight into 1) the extent to which the four pillars of the SUPREMOCOL protocol are implemented in clinical practice as intended, 2) the proportion of settings and practices that adopted the SUPREMOCOL study into their clinical practice, and 3) the proportion of the target population that participated in the SUPREMOCOL study.

### Allocation

If possible, block-wise randomisation will be performed to determine the starting order of the SMHI areas. The ‘blocks’ of areas will be based on the SMHI’s level of implementation and organization, as the implementation of the intervention requires a lot of preparation from the SMHI’s. The block-wise randomization will take place in three steps. First, the SMHI will receive a proposal regarding the implementation of the intervention. Six criteria indicate the extent to which the SMHI is ready for the implementation of SUPREMOCOL. The six criteria are that the SMHI: 1) has a contact person that will be involved in preparing the SMHI for implementing the intervention, 2) provides permission from the board to start the implementation, 3) has set up a team that will provide the daily check for new enrolments in the monitoring system, including providing a first contact with the person, 4) has set up a team that will provide monitoring contacts to the people registered, 5) has received the instructions for working with the monitoring system, and 6) has tested the monitoring system. Second, three blocks will be created, based on the organizations’ level of implementation and organization. Therefore, the three blocks will be: ‘replies to the proposal and is ready to start with the implementation’ (group a), ‘replies to the proposal and is not yet ready to start with the implementation’ (group b) and ‘does not reply to the proposal’ (group c). Third, randomization will take place within the SMHI’s which belong to block a. In this manner, the remaining organizations have extra time to prepare for implementation. If there is only one SMHI in a group, the SMHI will be randomized with a dummy. The districts will be randomized by an independent statistician using a computer algorithm for randomization.

### Outcomes

The primary outcome of this study is completed suicides and the secondary outcome is suicide attempts. Suicidal ideation will, if possible, be an exploratory process measure. Moreover, the impact of the intervention and intervention integrity will be measured. The outcomes and their data collection methods are discussed below.

### Primary outcome: completed suicides

The primary outcome of this study is completed suicides. In the Netherlands, the occurrence of completed suicide is registered by coroners in the ORION system. The records from the ORION system regarding Noord-Brabant will be obtained from the Regional Public Health Institutes (PHI [in Dutch: Gemeentelijke Gezondheidsdienst; GGD]): GGD Brabant-Zuidoost, GGD West-Brabant, and GGD Hart voor Brabant. The PHI’s report their records to Statistics Netherlands, who collect the records for the whole country and make corrections if needed. To evaluate whether SUPREMOCOL leads to a reduction of completed suicides of 20% in the province of Noord-Brabant (hypothesis 1), completed suicides will be assessed during a one-year pre-post measurement for the total population of the province of Noord-Brabant. The pre-measurement will take place in the year before any of the areas in Noord-Brabant have entered the roll-out period (thus: 1 year before the start of period 1 of the SWT; therefore including period 0 of the SWT), and the post-measurement will take place in the year after implementation in all areas (thus: after period 5 of the SWT). National records from Statistics Netherlands will also be used for the pre-post evaluation, as completed suicide rates will be compared in time (pre-post) and per region (Noord-Brabant versus other provinces in the Netherlands). As it is also hypothesized that SUPREMOCOL leads to a reduction of completed suicides and suicide attempts in association with the stepwise implementation of the system intervention in the subregions of the province (hypothesis 2), completed suicides will also be assessed during the stepped wedge trial in the subregions of Noord-Brabant. Regional PHI records will be used for the SWT evaluation. For this, the total number of completed suicides per month will be examined.

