**Methods/design:**

Study protocol. A regional suicide prevention systems intervention is implemented and evaluated by a stepped wedge trial design in five specialist mental health institutions and their adherent chain partners. Our system intervention is called SUPREMOCOL, which stands for Suicide Prevention by Monitoring and Collaborative Care, and focuses on four pillars: 1) recognition of people at risk for suicide by the development and implementation of a monitoring system with decision aid, 2) swift access to specialist care of people at risk, 3) positioning nurse care managers for collaborative care case management, and 4) 12 months telephone follow up. Eligible patients are persons attempting suicide or expressing suicidal ideation. Primary outcome is number of completed suicides, as reported by Statistics Netherlands and regional Public Health Institutes. Secondary outcome is number of attempted suicides, as reported by the regional ambulance transport and police. Suicidal ideation of persons registered in the monitoring system will, be assessed by the PHQ-9 and SIDAS questionnaires at baseline and 3, 6, 9 and 12 months after registration, and used as exploratory process measure. The impact of the intervention will be evaluated by means of the RE-AIM dimensions reach, efficacy, adoption, implementation, and maintenance. Intervention integrity will be assessed and taken into account in the analysis.

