#### Sample size

The sample size calculation is based on completed suicide rates, as this is the primary outcome of this study. The USA study of which we adapted our systems approach established a drop in potentially salvageable deaths from 34% (20/58) to 15% (9/60) (*p* < .02) following implementation, which is a Hazard Ratio of 2.3. We assume that in trauma patients, compliance of patients with entrance to care, if provided, was 100%, as the trauma is a one-time occurrence and involuntary. In people at risk for suicide, this risk may be sustained for a longer period of time, require multiple entrances into care and compliance may not always be the case. Hence, we want to be able to detect a smaller difference, which is of 20% in the completed suicides, as specified in our hypothesis. This corresponds to a rate ratio of 1.25. Based on an alpha of 0.05 (two-sided) and a power of 0.80, for this purpose, the minimal number of events would be 184 in each year. As completed suicides are the primary outcome we do not expect any loss to follow up for that outcome. As in 2017, the number of completed suicides in Noord-Brabant reported by Statistics Netherlands was 365, and all relevant settings in the region will collaborate, we expect that it will be feasible to find a difference of 20% in completed suicides, if such a difference exists, with an alpha of 0.05 and a power of 0.80.

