#### Statistical methods

To examine whether SUPREMOCOL leads to a reduction of completed suicides of 20% in the province of Noord-Brabant, the total number of completed suicides in the post-measurement will be compared to the total number of completed suicides in the pre-measurement. As the total number of residents in this province might have changed, we will also compare the pre- and post-incidence rates of suicides. An exact rate ratio test will be used. To take general trends over time into account, we will compare the incidence ratio in Noord-Brabant with the incidence ratios in other provinces in Noord-Brabant, and with the other provinces combined.

To examine whether SUPREMOCOL leads to a reduction of completed suicides and suicide attempts in association with the stepwise implementation of the system intervention in the subregions of the province, the total number of completed suicides and suicide attempts in each month will be compared to the two levels of our stepped wedge trial: region and time. A poison multilevel model will be used. The occurrence of completed suicide or admissions due to suicide risk in an SMHI will also be taken into account in the analysis. The suicide rates will be corrected for seasonal fluctuations [45]. In a second model, organisational differences between the regions, such as available number of crisis departments, will be taken into account. In a third model, the level of treatment integrity per subregion will be taken into account as well.

To explore whether SUPREMOCOL leads to a reduction of suicidal ideation in people registered in the monitoring system, the scores on the PHQ-9, SIDAS, and decision aid -that will be filled out by participants during the year that they receive the Supremocol additional care- will be compared by repeated measures. This will be used as exploratory process evaluation, as there is no control group for this.

To examine the impact of SUPREMOCOL with regards to reach, efficacy, adoption, implementation, and maintenance, an impact score will be calculated for each SMHI region and time period. This scores will be based on the function of all five RE-AIM dimensions, which are represented on a 0% (no impact) to 100% (best possible impact) scale [43].

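### Completed suicides is tested by both a province pre-post comparison and a stepped wedge model, and the protocol points both ways on which one decides

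*Protocol article*

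**What the plan says.** The Outcomes section ranks outcomes, not analyses: "The primary outcome of this study is completed suicides and the secondary outcome is suicide attempts". Under the heading for the primary outcome, two evaluations follow.

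- **Hypothesis 1:** "completed suicides will be assessed during a one-year pre-post measurement for the total population of the province of Noord-Brabant". National records are added so that the change can also be set against the other provinces. The Statistical methods section gives the test: "An exact rate ratio test will be used".
- **Hypothesis 2:** "completed suicides will also be assessed during the stepped wedge trial in the subregions of Noord-Brabant", using monthly counts. The method is "A poison multilevel model will be used", with region and time as levels and a correction for season.

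The signals on which one decides differ. The abstract says: "A regional suicide prevention systems intervention is implemented and evaluated by a stepped wedge trial design". The section on the stepped wedge design and the opening of the Discussion say the same. The Sample size section, however, counts events per year: "Based on an alpha of 0.05 (two-sided) and a power of 0.80", it asks for 184 events in each year and sets against this the 365 suicides recorded in 2017. That describes the pre-post comparison only. No section gives an order of testing, a division of alpha, or a reading for the case where one test is significant and the other is not.

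**The concern.** Which analysis decides the primary outcome is a protocol-level matter. This article states the hypotheses, tests, alpha and sample size itself, and they do not agree on it. The two tests draw on nearly separate information. The pre-post test uses change over calendar time in the whole province. A wedge model that adjusts for time uses differences between regions within the same period. Two things are at stake:

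- After the data are in, the choice of the test that counts would be open. If a positive result on either could be reported as efficacy on the primary outcome, the stated 0.05 would not hold.
- A split result is likely even if the intervention works as hypothesised, and the plan does not say what the trial would then conclude.

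**Working it through.** **Inputs from the protocol.** 365 suicides a year, 20% reduction, two-sided alpha 0.05, power 0.80 and 184 events a year (Sample size); five clusters (Stepped wedge trial design); three-month periods (Public health impact). The pre-year includes period 0 and the post-year starts after period 5 (Primary outcome).

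**Assumptions.** Immediate full effect, no overdispersion, normal approximation, period 0 of three months (Fig. 4 is not shown). Region shares are equal, or 35/25/20/12/8%.

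**1. The plan's own figure.** A one-sample Poisson score formula with the pre-year rate taken as known gives (1.960 + 0.8416 × √0.8)² / 0.2² = 183.97, so 184. This confirms that the sizing concerns yearly province counts and not the wedge. The planned test compares two observed years and needs about 355 pre-year and 284 post-year events. That is a separate point, and the expected 365 still suffices, as step 2 shows.

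**2. Pre-post power at a rate ratio of 0.80.** Post-year events: 0.8 × 365 = 292. SE of the log rate ratio = √(1/365 + 1/292) = 0.0785. Power = Φ(ln 1.25 / 0.0785 − 1.96) = Φ(2.84 − 1.96) = 0.81; the exact test gives 0.80.

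**3. Wedge power.** With region and period effects over periods 0 to 5 and equal regions, the Poisson information matrix gives SE 0.162. Power = Φ(0.223 / 0.162 − 1.96) = Φ(−0.58) = 0.28.

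**4. Correlation.** With period effects, the wedge estimate's weights cancel within every period, so its covariance with province totals is zero, although period 0 is shared.

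**5. Error if either test sufficed, at correlation 0.** Two-sided: 1 − 0.95² = 0.0975. False benefit: 1 − 0.975² = 0.049, against 0.025 for one test.

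**6. Disagreement at a rate ratio of 0.80, at correlation 0.** Both significant: 0.81 × 0.28 = 0.23. Exactly one: 0.81 + 0.28 − 2 × 0.23 = 0.63 (0.64 unrounded). Pre-post alone makes up most of it: 0.81 × 0.72 = 0.58.

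**7. Sensitivity to the wedge model.** All rows have region effects; ranges cover equal and unequal regions. The either and false-benefit columns are under no effect; the last two columns are at a rate ratio of 0.80.

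| Time terms | Window | Correlation, no effect | Either, two-sided | False benefit | Wedge power | Exactly one |
|---|---|---|---|---|---|---|
| Period effects | 0–5 | 0.00 | 0.0975 | 0.049 | 0.26–0.28 | 0.64–0.65 |
| Period effects | 0–6 | 0.00 | 0.0975 | 0.049 | 0.28–0.30 | 0.62–0.64 |
| Period effects | pre-year to post-year | 0.00 | 0.0975 | 0.049 | 0.34–0.37 | 0.58–0.60 |
| Linear trend + season | 0–5 | 0.01–0.05 | 0.097 | 0.049 | 0.28–0.29 | 0.63 |
| Linear trend + season | 0–6 | −0.01–0.01 | 0.0975 | 0.049 | 0.32 | 0.61–0.62 |
| Linear trend + season | pre-year to post-year | 0.01–0.03 | 0.0975 | 0.049 | 0.47 | 0.52 |
| Season only | 0–5 | 0.15–0.18 | 0.097 | 0.049 | 0.58 | 0.42 |
| Season only | 0–6 | 0.23 | 0.096 | 0.048 | 0.61–0.65 | 0.36–0.39 |
| Season only | pre-year to post-year | 0.81–0.82 | 0.077–0.078 | 0.039 | 0.94 | 0.15 |

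A simulation (4,000 trials per scenario, periods 0 to 5, period effects) agrees. The chance of either test rejecting was 0.094 with region effects and 0.102 without. Wedge power was 0.28 and 0.44, and disagreement 0.62 and 0.53.

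**8. Secular trend.** With no intervention effect but a 10% province-wide fall, the pre-post test shows a significant benefit with probability Φ(0.105 / √(1/365 + 1/328.5) − 1.96) = Φ(1.385 − 1.96) = 0.28.

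**The case against.** A reader might infer that the protocol grants the trial two chances to claim success and so runs at an error near 0.10. The text does not support that. It contains no either-test rule, and alpha appears only in the sample size. The two hypotheses also ask different questions: a fall in the province, and an association with the stepwise roll-out.

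The text also leans one way. The provincial 20% reduction comes first, carries number 1, is the project's objective, and is the only hypothesis with a power calculation; the wedge is introduced as an addition. Rules for multiplicity can be left to an analysis plan that is not shown here.

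Much of this stands. The error figures are conditional. The two-sided figure of about 0.10 includes false harm, so 0.049 against 0.025 is the fair measure of a false efficacy claim. Disagreement depends on the wedge model, arises mainly from unequal power, and does not fall when one test is named. The figures also come from fixed-effect Poisson models, not from the planned multilevel model.

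What the objection does not remove is the conflict. A lean is not a statement, and the abstract, design section and Discussion lean the other way. The wedge analysis of suicides is never called secondary or supportive, although attempts are called secondary and ideation exploratory.

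**Conclusion.** The point holds as an unresolved conflict over the decisive analysis, not as a demonstrated breach of alpha. If either test may support efficacy, the two-sided error is about 0.08 to 0.10, and false benefit is about 0.049 when the tests are independent. At the hypothesised effect, a split result is the likeliest outcome when the wedge model adjusts for time (52 to 65%). It is less common with season only (36 to 42%) and uncommon (15%) if the full pre-year and post-year enter with no trend. The cause is mainly wedge power of about 0.26 to 0.47 in the time-adjusted models against about 0.80. All of this rests on 365 suicides a year, five regions, three-month periods, an immediate effect and no overdispersion. Extra variation between cluster-periods would lower wedge power further.

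**What to change.** In the Hypotheses, Primary outcome and Statistical methods sections, name one analysis of completed suicides as decisive at two-sided 0.05.

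- The hypothesis numbering and the sample size point to the pre-post comparison of incidence rates. If it is chosen, state that a positive conclusion must also be read against the change in the other provinces. Hypothesis 1 already requires this, and the within-province comparison alone is open to secular trend (working, step 8). The Discussion itself notes that other prevention initiatives run at the same time.
- Test the other analysis second in a fixed sequence, or label it supportive and report an estimate with a 95% CI.
- State how discordant results will be read.

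The cost is wording only. The downside is that a lone positive result on the non-decisive analysis can no longer be claimed as primary efficacy. The change settles how a split result is read but does not make one less likely.
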